## Abstract

**Background:**

Cancer-related fatigue is one of the most common symptoms experienced by cancer patients, and it diminishes their quality of life. However, there is currently no confirmed standard treatment for cancer-related fatigue, and thus, many patients who suffer cancer-related fatigue seek complementary and alternative medicines such as moxibustion. Moxibustion is one of the most popular therapies in traditional Korean medicine used to manage fatigue. Recent studies have also demonstrated that moxibustion is effective for treating chronic fatigue. However, there is insufficient evidence supporting the effect of moxibustion against cancer-related fatigue. The aim of this study is to assess the efficacy and safety of moxibustion treatment for cancer-related fatigue.

**Methods/design:**

A multi-center, three-armed parallel, randomized controlled trial will be conducted. Ninety-six patients with cancer-related fatigue will be recruited from three clinical research centers. They will be randomly allocated to one of three groups in a 1:1:1 ratio. The moxibustion group will receive moxibustion treatment at CV8, CV12, LI4 and ST36. The sham moxibustion group will receive sham moxibustion at non-acupoints. Both the moxibustion and sham moxibustion groups will receive 30-min treatments twice a week for 8 weeks. The usual care group will not receive moxibustion treatment. All participants will be educated via a brochure on how to manage cancer-related fatigue in daily life. The outcome measurements will be evaluated at baseline, week 5, week 9, and week 13 by assessors who are blinded to the group allocation. The primary outcome measure will be the mean change in the average scores of the Brief Fatigue Inventory before and after treatments between groups. The secondary outcome measures will be the mean difference in changes from baseline of the Brief Fatigue Inventory, functional assessments of cancer therapy-fatigue, European Organization for Research and Treatment of Cancer Quality of Life Questionnaire C-30 scores, and Montreal Cognitive Assessment scores between groups. Safety will be assessed by monitoring adverse events at each visit.

**Discussion:**

The results of this study will provide evidence to confirm whether moxibustion can be used as a therapeutic option for treating cancer-related fatigue.

**Trial registration:**

Clinical Research Information Service KCT0002170. Registered 16 December 2016.

**Electronic supplementary material:**

The online version of this article (doi:10.1186/s12906-017-1856-3) contains supplementary material, which is available to authorized users.

## Background

As the prevalence of cancer and the survival rate of patients increase, the quality of life (QOL) of cancer survivors and the symptoms affecting QOL are gaining increased attention [1]. Cancer-related fatigue is one of the most common symptoms that cancer patients experience [2] and is among the most prominent residual or persistent symptoms of cancer survivors [3]. Cancer-related fatigue often occurs during the cancer treatment period, although it may occur independent of treatment and sometimes continues to persist even after the end of treatment or the complete remission of cancer [4].

Cancer-related fatigue reduces the level of energy and decreases the QOL of cancer patients, negatively affecting the return-to-work rate of cancer survivors [5, 6]. It also seriously damages the QOL of the families in addition to cancer patients in terms of physical, social, economic, psychological and spiritual aspects [7]. However, it is not a fatal condition that directly threatens the survival of cancer patients. Therefore, it is recognized to be relatively less important than other critical issues regarding cancer [8]. Moreover, the definition of cancer-related fatigue is completely dependent on the subjective sense of tiredness felt by the patient, and therefore, it is easy to overlook when the patient does not actively report the symptom [8].

The mechanism of cancer-related fatigue has been reported to be associated with cytokine production or mediators of inflammatory responses of cancer and/or cancer treatment [9]. In particular, tumor necrosis factor (TNF) alpha signaling seems to be closely related to cancer-related fatigue [6]. In addition to inflammation and latent viral reactivation [10, 11], other various factors such as oxidative stress [12], changes in the neuroendocrine system including dysregulation of the hypothalamic-pituitary-adrenal (HPA) axis, autonomic nervous system disorders including central vagal stimulation, serotonin dysregulation [10, 11], and changes in muscle and ATP metabolism [11], have been reported to be involved in cancer-related fatigue. However, the mechanism of cancer-related fatigue has not yet been fully elucidated [13].

There are various known risk factors related to cancer-related fatigue, including the stage of cancer, the specific type of cancer (breast, colon, liver) and diabetes, high body mass index, genetic factor, psychological and biobehavioral factors such as the level of fatigue before cancer treatment, depression, sleep disturbances, physical activity and physical deconditioning, negative expectation, etc. [10, 14, 15]. The cancer itself, various cancer treatments, and accompanying diseases such as anemia, cachexia, etc., also appear to be related to cancer-related fatigue, but the degree of their contributions and how such risk factors interact remain unclear [11]. To date, the cause of cancer-related fatigue has not been explicitly identified [11, 14].

The first step in managing cancer-related fatigue is determining the possible causes of fatigue and correcting them [4, 8, 16]. However, as previously discussed, a variety of factors are involved and contribute to cancer-related fatigue, and therefore, it is very difficult to identify specific causes and to completely eliminate fatigue among cancer patients [14]. There is currently no standard therapy for treating cancer-related fatigue [6, 17].

For pharmacologic therapy to mitigate cancer-related fatigue, antidepressants and psychostimulants such as methylphenidate, modafinil, and bupropion and steroids such as dexamethasone have been proposed and studied, but the results of clinical trials are inconsistent [4, 16–18]. According to a recent meta-analysis, methylphenidate was significantly better than placebo, while the effect of modafinil was similar to that of placebo, although further studies are needed to confirm this conclusion [17]. Considering that the clinical effects of these drugs are unclear and the risk of adverse drug reactions are of high concern, especially for long-term use, no specific drug is currently recommended as a primary therapeutic option for cancer-related fatigue [17, 19, 20].

Despite the lack of a standard therapy for cancer-related fatigue, the high number of patients who suffer from cancer-related fatigue has created a demand for complementary alternative medicine (CAM). A systematic review reported that CAM utilization rates among cancer patients range from 11 to 95% [21]. According to a survey targeting breast cancer survivors in the United States, one third of patients used CAM [22]. Another survey conducted among South Korean cancer patients reported that more than half of respondents used CAM [23].

Moxibustion is one of the most commonly used treatments in traditional medicine in East Asia including Korea. It has been used to prevent and treat various diseases by warming the body and promoting the energy of patients [24, 25]. Moxibustion is particularly good at supplementing energy (*qi*), and thus, it has been often applied to patients who experience fatigue or similar conditions [25]. Modern scientific studies also have shown that moxibustion is effective in alleviating chronic fatigue [26–28], and some parts of its mechanism have been reported to be related to activation of the vagus nerve [26], reduction of oxidative damage [26, 27, 29], improvement of inflammation [30], regulation of the HPA axis [10], and upregulation of hippocampal progranulin [10].

Lee et al. [31] showed the possibility of using moxibustion to treat cancer-related fatigue through a systematic review and meta-analysis of related literature. However, all the studies included in this review were reported and conducted only in China, and most of the studies had high risk of bias. The details of moxibustion treatment used in each study were not described based on the Consolidated Standards of Reporting Trials (CONSORT) or on the Standards for Reporting Interventions in Clinical Trials of Acupuncture (STRICTA), and most of the studies did not report of adverse events (AEs) and drop-outs. Thus, Lee et al. [31] concluded that a well-designed clinical trial with better reporting quality is warranted to draw any conclusion regarding the effect of moxibustion for treatment of cancer-related fatigue. Recently, Mao et al. [32] demonstrated that their newly devised method of infrared laser moxibustion was more effective in reducing the level of fatigue than sham moxibustion. However, infrared laser moxibustion is not yet commonly used in Korea. More evidence is needed to confirm the effectiveness and safety of moxibustion against cancer-related fatigue.

Therefore, we designed this randomized controlled trial to compare the clinical responses of moxibustion, sham moxibustion, and usual care interventions in patients with cancer-related fatigue.

## Methods/design

### Design

This is a multi-center, three-armed parallel, randomized controlled trial. Ninety-six participants who meet the diagnostic criteria for cancer-related fatigue of the international classification of diseases, tenth revision clinical modification (ICD-10-CM), will be randomly allocated to one of the three groups in a 1:1:1 ratio. One group will be the treatment group (moxibustion group), and the other two will be control groups (sham moxibustion group and usual care group). The flowchart of this trial is shown in Fig. 1.

**Fig. 1 Fig1:**
[figure not shown]
Flow chart of the study

### Recruitment

Three clinical research centers in South Korea will recruit participants: Daejeon Oriental Hospital of Daejeon University, Kyung Hee University Oriental Hospital at Gangdong, and Dongguk University Bundang Oriental Hospital.

To ensure enough patients, clinical trial information will be posted on notice boards of the hospitals both on and offline. Recruitment notices will also be released on flyers, daily local newspapers, and advertisement boards at public places.

### Eligibility criteria

#### Inclusion criteria

Male or female aged 19 or over but under 80 yearsCessation of cancer-related treatments (e.g., surgery, chemotherapy, radiotherapy, immunotherapy) at least 12 weeks before the trial (on-going hormone therapy, which must have been initiated at least 3 weeks prior to enrollment, is allowed)Continuous fatigue related to cancer treatment or cancer itself for at least 4 weeks, fulfilment of the ICD-10-CM diagnostic criteria for cancer-related fatigue, and a brief fatigue inventory (BFI) score of 4 or moreAn Eastern Cooperative Oncology Group (ECOG) performance status ≤2Willingness to participate in the trial and having provided written consent

#### Exclusion criteria

Having maintained the current level of fatigue prior to the diagnosis of cancerSevere anemia (platelet count <60,000/μL, hemoglobin <8 g/dL, or absolute neutrophil count <1000/μL)Receiving aggressive treatment for anemia (e.g., erythropoietin or blood transfusion)Poor oral intake with a lower-than-normal level of serum albuminAny significant sign or symptom of inflammation with C-reactive protein (CRP) ≥ 10 mg/L and white blood cell >10,000/μLAbnormal findings in a thyroid function test (abnormal level of free thyroxine and thyroid stimulating hormone <0.1 μIU/ml or TSH > 5.1 μIU/ml)Abnormal findings in a liver function test or a renal function test (aspartate aminotransferase or alanine aminotransferase ≥2× upper normal range or creatinine ≥2.0 mg/dL) or the presence of serious liver failure or renal failureA score of 11 points or more on either the anxiety or depression subscales of the Hospital Anxiety and Depression Scale (HADS)An insomnia severity index (ISI) score of 15 points or moreLevel of cancer pain measured by the numeric rating scale (NRS) ≥ 4An estimated life expectancy of six months or lessA plan of surgery, chemotherapy, or radiotherapy during the studyHistory of medication (methylphenidate, modafinil, bupropion, dexamethasone) to manage cancer-related fatigue taken within 4 weeks of the beginning of the trialHistory of Korean medical treatment (e.g., acupuncture, moxibustion, cupping, or herbal medicine, etc.) to manage cancer-related fatigue within 4 weeks of the beginning of the trialInitiation or a change in dietary supplement regimen or non-pharmacologic therapies (e.g., cognitive behavioral therapy, exercise, etc.) for alleviating cancer-related fatigue during the trial or within 4 weeks of the beginning of the trialHaving participated in other clinical trials within 4 weeks of the beginning of the trialHistory of hypersensitivity reactions or serious adverse reactions (SAEs) after moxibustion treatment or an inability to cooperate with moxibustion treatment due to other reasons such as dyspneaWomen who are pregnant, lactating, or planning to become pregnantPresence of other apparent factors or any diseases that could cause current fatigue other than cancer treatment or the cancer itself

### Randomization and allocation concealment

Random numbers will be generated by SAS (Version 9.4, SAS institute. Inc., Cary, NC) and sealed in sequentially numbered opaque envelopes. The envelopes will be delivered to each research center and kept in a double-locked cabinet. The practitioners of each research center will open the envelops and allocate the participants who meet the eligibility criteria after signing an informed consent to one of the three groups according to the contents of the envelops.

### Blinding

Practitioners cannot be blinded because of the unique nature of moxibustion treatment. Although the subjects of the usual care group will be able to determine which group they are allocated to, the participants in the moxibustion and sham moxibustion groups will be blinded. To assess whether the patient-blinding was successfully achieved among the moxibustion group and sham moxibustion group, the subjects of these two groups will undergo a blinding test and a credibility test after the first and final treatment. Outcomes will be assessed by researchers who are not involved in the intervention procedure. Thus, the assessors will be blinded to all three groups, while the participants will be blinded in only the moxibustion and sham moxibustion groups.

### Intervention

There are three arms in this trial. All participants regardless of their assignment will be educated via a brochure on how to manage daily life to alleviate the cancer-related fatigue.

#### Moxibustion group

Participants in the moxibustion group will receive moxibustion treatment via two types of moxibustion devices: an ignition-type moxibustion device (IM, Fig. 2) and an electrical moxibustion apparatus (EM, Fig. 3).

**Fig. 2 Fig2:**
[figure not shown]
Ignition-type moxibustion device. **a**, safety cap; **b**, body of the device; **c**, mugwort moxa cone; **d**, the assembled device of **a**, **b**, **c** and **d**

**Fig. 3 Fig3:**
[figure not shown]
Electrical moxibustion apparatus. **a**, twelve moxibustion devices in a charger; **b**, a powered-up moxibustion device; **c**: the bottom of the moxibustion device embedded with an electrically heating board

The IM is composed of a red clay body covered by a silicon sheath and safety cap (Fig. 2). An ignited mugwort moxa cone will be inserted into the body of the IM. The base of the body has tiny holes that acts as a heat channel. Two IMs will be sequentially applied at two acupoints on the abdomen, CV8 and CV12 (Fig. 4).

**Fig. 4 Fig4:**
[figure not shown]
Acupoints for the moxibustion group

The EM is a cube-shaped apparatus with a base embedded in an electrical board controlled by a heat sensor (Fig. 3). The EM can be stably fixed on the body by attaching double-sided medical tape to the base of the EM. Four EMs will be sequentially attached at acupoints on the hands and legs, bilateral LI4 and ST36 (Fig. 4). When the button on the top of the EM is pushed, the board on the base starts to emit heat and the light on the top begins to blink. The plateau temperature of the base of the EM is 45 °C. The treatment time is 30 min, and the participants in this group will receive the treatment twice per week for 8 weeks. Detailed explanations of the moxibustion treatments are tabulated according to the revised STRICTA checklist for moxibustion (Additional file 1).

#### Sham moxibustion group

The appearances of the IM and EM used for the sham moxibustion group will be exactly identical to those used for the moxibustion group (Fig. 5). The participants will be able to see the practitioner ignite the mugwort and the IM with a small amount of smoke and burning odor applied on their abdomen. In the case of the EM, the participants will be able to see that the EM attached on their skin is turned on as the light on the top of the EM begins to blink. These procedures will be the same as the method used for the moxibustion group.

**Fig. 5 Fig5:**
[figure not shown]
A front view of moxibustion. **a** & **b**, ignition-type moxibustion devices; **a**, real; **b**, sham; **c** & **d**: electrical moxibustion apparatus; **c**, real; **d**, sham. The front views of the real and sham moxibustion devices are identical

However, the base of the IM will be filled with insulator made of styrofoam, and the heat sensor in the electrical board of the base of the EM will be controlled to block heat transfer (Fig. 6). The sham moxibustion will be applied at non-acupoints that are irrelevant to fatigue. The locations of the points that will be used for this group are as follows (Fig. 7): abdomen (approximately 13.5 cm above the bilateral 3 cm from the umbilicus), upper limb (1 cm lateral and 5 cm distal to the cubital creases of the bilateral arms), and lower limb (upper 1/3 points of the medial line of the bilateral tibia). The sham IMs will be applied on the abdomen points, and the sham EMs will be attached on the upper and lower limb points.

**Fig. 6 Fig6:**
[figure not shown]
A bottom view of moxibustion. **a** & **b**, ignition-type moxibustion devices; **a**, real; **b**, sham; **c** & **d**: electrical moxibustion apparatus; **c**, real; **d**, sham

**Fig. 7 Fig7:**
[figure not shown]
Non-acupoints for the sham moxibustion group

#### Usual care group

The participants in the usual care group will not receive moxibustion treatment. They will maintain their usual treatment and self-care but will not begin any additional treatment to improve their cancer-related fatigue during the study.

### Prohibited and permitted concomitant treatment

The participants will be prohibited from receiving any pharmacologic treatment of Western medicine or any other interventions of traditional Korean medicine to manage cancer-related fatigue other than the interventions provided by the trial. If they continued to receive other nonpharmacologic therapies such as exercise, yoga, meditation, etc. or were already taking any dietary supplements to mitigate cancer-related fatigue at least 4 weeks before the trial was initiated, they will be able to maintain the therapies. However, any treatment used to attenuate cancer-related fatigue cannot be newly introduced after the initiation of the trial. All new treatments begun after the beginning of the trial and concomitant medications to treat medical conditions unrelated to cancer-related fatigue will be recorded on the case report form.

### Study schedule of enrolment, allocation, and assessments

After eligibility screening of the candidate participants who had signed informed consent, the participants will be randomly allocated to one of the three groups. Before the initial intervention begins, baseline measures will be obtained. After four weeks of intervention, outcomes reflecting the level of fatigue will be assessed at week 5. Post-treatment assessments will be conducted at week 9 after completing eight weeks of intervention. The follow-up visit will be planned at week 13, concluding the trial. The schedule of the enrolment, interventions, and assessments is given in Table 1.

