#### Primary outcome measure

The mean change in average BFI scores from baseline to the end of the 8-week intervention will be the primary outcome measure of the study. The BFI is a questionnaire composed of 9 questions related to the degree of fatigue and the level of daily life interference caused by the fatigue [33]. Zero to ten points are assigned to each question (0 = no fatigue or no interference; 10 = the most severe level of fatigue or complete interference). The level of the fatigue can be grouped into three categories according to the average BFI score: 1–3 (mild), 4–6 (moderate), 7–10 (severe) [33].

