**The alternative hypothesis (H**
_**12**_
**):** There is a difference in the mean change of the BFI before and after treatment between the moxibustion group and the sham moxibustion group.

To test the two hypotheses, analysis of covariance (ANCOVA) will be utilized with the baseline BFI value as a covariate and each group as a fixed factor. If any clinically significant difference between groups is identified among the demographic characteristics or the variables measured at baseline, it will be adjusted based on its covariance. The problem of multiple comparison will be solved using the fixed sequence method. In other words, if the H_01_ is rejected and H_11_ is adopted in the statistical test for the first hypothesis set, and then the test for H_02_ will performed. However, when the H_01_ is adoptted, the second hypothesis set for H_02_ will not be verified [42].

The secondary outcome measures of the study will be the mean changes in the BFI, FACT-F, EORTC QLQ C-30 and MoCA before and after the interventions in the three groups. They will be analyzed via the same methods used for the primary outcome measure analysis. Student’s paired t-tests or Wilcoxon signed-rank tests will be used to analyze the differences in the measured values before and after treatment in each group. ANOVA with Dunnett’s post hoc test will be performed to compare the differences in trends per visit. Subgroup analyses will be conducted to check whether there are significant differences in the responses to moxibustion treatment depending on the severity of fatigue, the expected level of treatment, or patterns of cold-heat and deficiency-excess measured at baseline.

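### As narrated, the self-reported baseline BFI is collected after allocation, so unblinded usual-care patients may complete it knowing their arm; this can bias the gatekeeping comparison with usual care.

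*Protocol article*

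**What the plan says.** The protocol article's section on the study schedule runs from consent and screening to allocation and then to baseline: "the participants will be randomly allocated to one of the three groups. Before the initial intervention begins, baseline measures will be obtained". It refers to Table 1 for the full schedule, and that table is not reproduced in the text at hand.

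Under Randomization and allocation concealment, the step that reveals the arm happens at the site: "The practitioners of each research center will open the envelops and allocate the participants who meet the eligibility criteria". Under Blinding, those practitioners are unblinded and "the subjects of the usual care group will be able to determine which group they are allocated to", whereas "the participants in the moxibustion and sham moxibustion groups will be blinded".

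The baseline BFI enters the primary analysis twice. Under Primary outcome measure: "The mean change in average BFI scores from baseline to the end of the 8-week intervention will be the primary outcome measure". Under Statistical analysis: "analysis of covariance (ANCOVA) will be utilized with the baseline BFI value as a covariate and each group as a fixed factor". The same section sets a fixed sequence in which moxibustion versus sham (H02) is tested only if moxibustion versus usual care (H01) is rejected.

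The inclusion criteria require a BFI of at least 4, so some BFI value must exist before the envelope is opened. Nothing says whether that value is the baseline.

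**The concern.** ANCOVA gives an unbiased treatment contrast in a randomised trial because the covariate cannot be influenced by the allocation. A questionnaire completed after the patient has learned the arm loses that protection. A usual-care patient who is disappointed may rate fatigue higher; a patient who expects nothing further from the trial might rate it lower. Blinded assessors do not help, because the patient supplies the score.

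The exposed contrast is mainly H01, since usual care is the only arm that can be identified with certainty. H01 is also the gatekeeper: if it is missed, the sham comparison is never tested.

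Other self-reported baselines are exposed in the same way: FACT-F, EORTC QLQ-C30 and the cold-heat and deficiency-excess pattern questionnaire used for subgroups. MoCA measures cognitive performance and is administered by blinded assessors, so it is less exposed.

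Unblinded reporting at follow-up cannot be avoided with a usual-care arm. At baseline it can.

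**Working it through.** **The plan's own figure.** Sample size calculation gives a difference of 1.6, SD 2.0, two-sided 5% and 80% power. n = 2 × [2.0 × (1.960 + 0.842) / 1.6]² = 24.5, rounded up to 25. Then 25 / 0.80 = 31.25, rounded up to 32, and 3 × 32 = 96. The figures reproduce, and this point does not depend on them.

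**The bias.** Let s be the shift in usual-care baseline BFI caused by knowing the arm, and let β be the slope of week-9 BFI on baseline BFI. Assume that the shift affects the baseline report only. Under no treatment effect:

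- Adjusted difference, moxibustion minus usual care = (difference in week-9 means) − β × (difference in baseline means) = 0 − β × (0 − s) = β × s.
- A plain change score would carry the full s, but the planned test is ANCOVA.

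Lower BFI is better. A positive s (usual care reports worse baseline fatigue) therefore makes moxibustion look worse, and a negative s makes it look better.

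**Inputs for illustration.** SD 2.0 is the protocol's figure. 26 per arm is 32 × 0.80 = 25.6, rounded up. The correlation of 0.5 and the values of s are assumptions; the protocol gives neither. If baseline and week 9 each have SD 2.0, a correlation of 0.5 gives β = 0.5 and an SD of change of 2.0 × √(2 × (1 − 0.5)) = 2.0, which agrees with the protocol.

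**Test of H01 under the null.** Residual SD = 2.0 × √(1 − 0.25) = 1.73. SE = 1.73 × √(2/26 + s² / 200), where 200 = 2 × 25 × 2.0² is the expected within-arm sum of squares of baseline in the two arms. Rejection comes from the noncentral t distribution with 49 df.

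| Shift s | Bias β × s | SE | Bias / SE | Total two-sided rejection |
|---|---|---|---|---|
| 0 | 0 | 0.480 | 0 | 5.0% |
| 0.3 | 0.15 | 0.482 | 0.31 | 6.1% |
| 0.5 | 0.25 | 0.484 | 0.52 | 8.0% |
| 1.0 | 0.50 | 0.496 | 1.01 | 16.7% |

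Simulation of the same setting agrees to within about half a percentage point.

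**Direction.** In 20,000 simulated trials per scenario, upward shifts of 0.3, 0.5 and 1.0 cut false rejections favouring moxibustion from the nominal 2.5% to about 1%, 0.6% and 0.2%. Nearly all of the excess is usual care appearing better. Downward shifts of the same sizes raise false rejections favouring moxibustion to about 4.8%, 7.0% and 16.4%.

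**Power.** Apply the protocol's 1.6-point effect to H01. This is an assumption, because the protocol states it for the sham contrast. Power is then about 90% with no shift, and about 83%, 77% and 58% with upward shifts of 0.3, 0.5 and 1.0.

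**Range over the slope.** With 25 per arm, SE = 2.0 × √(2/25) = 0.566 (taking 2.0 as the residual SD, which is conservative) and a normal approximation, β from 0.3 to 0.7 gives total rejection of 5.2% to 6.1% at s = 0.25, 5.8% to 9.5% at s = 0.5, and 8.3% to 23.6% at s = 1.0.

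**The case against.** The order is inferred from consecutive sentences in a condensed article. The baseline sentence itself sets only a latest time, and Table 1 could show baseline before allocation. This stands as a limit on certainty. If Table 1 does show that, the narrative still needs correcting to match, because no other text places baseline before allocation.

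The protocol does not say when patients are told their arm. Practitioners open the envelopes, and a usual-care patient might complete the BFI before learning the result. This also stands: patients may know, but the text does not show that they do.

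A screening BFI must exist before allocation. That makes the repair easy, but it does not answer the point while no text makes it the baseline.

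The Discussion already concedes possible bias from unblinded usual-care patients. It does so for subjective outcomes in general and does not deal with a baseline reported after allocation.

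A reader might infer that the plan inflates false claims of efficacy. The documents do not support that. They give no shift and no direction, and under the disappointment mechanism false claims for moxibustion become rarer and the harm is lost power. A reader might also infer that the sham comparison is biased. Both device arms are meant to be blinded to real versus sham, so that estimate is largely untouched; it is at risk only through the gatekeeping.

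**Conclusion.** The point holds as a conditional risk. Followed as written, the schedule allows the covariate and starting value of the primary outcome to be reported after unblinded patients learn their arm. The bias in H01 is about slope × shift. Under an assumed correlation of 0.5 and shifts of 0.3 to 1.0 points, that is 0.15 to 0.50 BFI points and roughly 6% to 17% total rejection under the null. At 0.3 the excess is only about one percentage point, and a shift of 1.0 is more than 60% of the planned 1.6-point effect (1.0 / 1.6 = 62.5%). The real size and direction are unknown. The result also rests on the narrated order being the order used and on the shift not carrying over to week 9. It should be corrected because the step is avoidable, touches the primary analysis and cannot be fully repaired once the data are collected.

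**What to change.** Reword the study schedule so that all baseline questionnaires, including the pattern questionnaire, are completed and filed before the envelope is opened. Record both times on the case report form. Check that Table 1 shows the same order.

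Alternatively, define the screening BFI required for eligibility as the baseline for both the change score and the covariate. This protects the primary outcome, but not the other questionnaires unless they too are collected before allocation.

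The Trial status section says that recruitment is under way. For participants already enrolled, check which came first, use the screening BFI where baseline followed allocation, and report how many this concerns.

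The cost is a small mid-trial clarification and possibly a mixed baseline definition for early enrolees. The screening value was also selected to be at least 4, so within-arm before-after changes measured from it would include some regression to the mean. That selection applies equally to all arms and does not bias the between-group contrast. The sample size does not change.
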